### 2.4. Data Collection and Variables under Study

Data collection will be performed through self-administered questionnaires, wearable devices for biomonitoring physiological signals (in association with a smartphone app), and direct observations of mother–child interactions. It will be conducted on five different moments (Figure 1): baseline (t_0_; 28–30 gestation weeks), one week after enrolment (t_1_; 29–31 gestation weeks), two weeks postpartum (t_2_), five months postpartum (t_3_), and twelve months postpartum (t_4_). Data collection will be performed by members of the research team. Women in the intervention group with biofeedback will wear a smartwatch to biomonitor several physiological signals combined with the use of a sleep analyzer device (for details, see Table 1). Both devices will communicate through Bluetooth with a datahub and send physiological data to the supplier’s cloud. The server will communicate on a regular basis, via a secure oAuth2 authentication method, with the supplier’s cloud and retrieve all data to be stored in a relational database including wearables-collected information, questionnaires filled in by the participants and health data gathered by healthcare professionals. Health indices computed out of these data will be made available to participants in their website/app private areas, alongside trend graphics and other simple although insightful data visualizations of relevant information such as sleep pattern, accelerometry, pulse rate, pulse rate variability, among others. The system to be developed will also support the project throughout its course, namely by generating reports on its evolution (e.g., successful contacts), listing scheduled contacts, and asking participants to fill in questionnaires, among others.

Strategies to reduce attrition during the experimental period will be implemented. At recruitment, pregnant women will be provided with detailed information about the project, including the objectives and participant’s role in the study. During post-allocation period, referrals to other healthcare professionals will be performed as necessary, and the required logistic support for data collection will be provided, such as scheduling suitable data collection appointments [69]. Reminders will be sent to enrolled women one week before the scheduled date of each data collection moment. Women in the intervention group with biomonitoring of physiological signals will receive tailored health-related information based on data collected through wearable devices (biofeedback), whereas women in both the control and intervention arms will receive general health information via a smartphone app (also accessible in the private area of the project’s website). This app will be developed specifically for MAMH@WORK project and will be available for download by all women enrolled in the study. It will mirror information available at the website and facilitate communication between the research team and participants. 

The main outcomes that will be used to assess the effectiveness of the intervention are women’s psychological wellbeing (mood disorders and anxiety disorders, assessed by the Hospital Anxiety and Depression Scale/HADS and by the Edinburgh Postnatal Depression Scale/EPDS), subjective wellbeing (Self-Report of Happiness), quality of mother–child interactions (assessed by the CARE-Index) and child-mother attachment (assessed by the Strange Situation Procedure and by the Postpartum Bonding Questionnaire/PBQ). Secondary outcomes include child emotional self-regulation and cognitive self-control; women’s job engagement and presenteeism; and women’s physiological signals (pulse rate, pulse rate variability, and sleep patterns).

In order to characterize the sample and adjust outcome indicators, sociodemographic data will be collected and will include women’s age, marital status, household size, educational level, main occupation, monthly income, and child’s gender. Women will be asked to characterize their workplace (e.g., company size, work–life balance policies, and workload) and to provide data on life events, such as previous miscarriages, divorce/loss of spouse, death of a close relative, serious illness diagnosis (of the mother, the child or of a close relative), moving out, and changes in household income. Additional moderation or mediation variables to be collected are mental health literacy, stress-related coping style, resilience, and quality of relationship with partner/husband, perceived support from partner/husband in childcare, kindergarten-related variables (e.g., time per day, and satisfaction with care), and job satisfaction before maternity leave.

All questionnaires to assess the constructs under study were selected taking into account their psychometric properties for the Portuguese population. Table 1 provides an overview of the instruments to be used under MAMH@WORK project.

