### 1.1. Return to Work after Childbirth

Maternal mental disorders impair the life of a woman as a whole, including her functioning in the workplace [13,39]. Healthy and motivated employees are fundamental at the organizational level and for the socioeconomic wellbeing of any country [40]. Engaged employees are less likely to experience absenteeism or presenteeism, thus contributing to increased productivity [41]. In addition to individual (e.g., health conditions, and resiliency) and family (e.g., spouse support, and financial strain) characteristics, the workplace in all its dimensions (i.e., interpersonal relations and group dynamics, organizational culture, productivity and quality/safety-related challenges, and external environment) represents a potentially major stress factor to employees [42].

During the postpartum period, many women return to paid work. Maternity leave in Portugal is of 42 mandatory days after childbirth. Portuguese parents are also eligible for 120 or 150 days of paid leave at 100% and 80%, respectively. The specificities of maternal and parental leave vary across the European Union-28. For example, German mothers are eligible for up to 42 non-mandatory days during the antenatal period and paid postpartum leaves of 56 mandatory days. In Sweden, parental leave is up to 240 days of paid plus unpaid leave until 18 months postpartum [43]. These differences in national legislation imply that, depending on the country, European women return to work at different stages of physical and psychological postpartum recovery.

Despite latent psychosocial benefits from being employed [44] and empirical evidence that women respond positively to returning to work after childbirth, recent mothers may perceive this moment as a stressful event [45]. In a qualitative study addressing the perceptions of recent mothers when returning to work within one year after childbirth, several resilience-related challenges were identified, the most common one being role conflict (i.e., the difficulty in balancing work and childcare responsibilities) [45]. This arises from three major forms of conflict between roles: time, strain- and behavior-based conflict [46]. For example, a full-time non-flexible work schedule reduces mother’s time with her child, whereas low levels of social support by either her co-workers or partner can result in conflict between work and childcare responsibilities.

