### 1.2. Aims and Objectives

The main aims of MAMH@WORK are: (a) to promote perinatal mental health, from the last trimester of pregnancy up to the first 12 months after childbirth, (b) to foster the healthy psychosocial and emotional development of children via an improved quality of early mother–child interactions, and (c) to reduce sickness absence and presenteeism of working-age women during this period. Considering these aims, the main goals of this project are to develop a maternal mental health and wellbeing promotion program and to evaluate its effectiveness. To achieve these goals, it is proposed the design, implementation and effectiveness assessment of a brief group cognitive-behavioral therapy-based (CBT-based) psychoeducation, including mindfulness e-training, combined with biofeedback. Specific objectives are to (a) design an intervention program to promote wellbeing and prevent perinatal mental disorders in Portuguese pregnant women; (b) develop a smartphone app that will provide women with targeted biofeedback based on the continuous (wearable-based) biomonitoring of selected physiological signals; and (c) assess the impact of the intervention on maternal perinatal mental health outcomes, on the interaction between mother and child (namely regarding the quality of mother–child interaction, child–mother attachment and child emotional self-regulation and cognitive self-control), and on the reduction of women’s absenteeism and presenteeism after childbirth.

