### 2.3. Description of the Intervention

The intervention will be developed in three phases: (1) a scoping literature review followed by a Delphi panel for consensus building on the contents and structure of a brief group CBT-based psychoeducation intervention, (2) the implementation and (3) effectiveness assessment of the intervention. In order to produce culture-specific recommendations for the intervention, Portuguese general practitioners, obstetricians, pediatricians, neurologists, psychiatrists, health and clinical psychologists, and nurses specialized in perinatal mental health care will be invited to take part in the Delphi panel, which will be informed by the scoping literature review.

The intervention will address maternal mental health and wellbeing protection and promotion during late pregnancy, postpartum and return to work. More specifically, it will target women’s psychosocial adjustment and resilience during this life stage, while promoting several strategic skills: recognition of signals and symptoms of mental disorders; reduction of stigma against mental disorders; coping skills for stressful situations, with a special focus on e-training of mindfulness; enhancement of help-seeking efficacy; and strengthening of emotional and cognitive self-regulation. It will follow a cognitive-behavioral and psychoeducational paradigm, and it is planned as a short-term group intervention of 20 h to be delivered in two blocks, one immediately before delivery and the other before returning to work. The first block will consist of two sessions, four hours each, whereas the second block will be organized into three sessions, four hours each. To better meet the objectives of this intervention, group size will not be larger than 15 women per session. Intervention block 1 will also include mindfulness exercises for coping with stress, and short videos with easy-to-follow exercises will be available at the private area of the website (details provided below). Block 2 will recap the main contents of block 1 and focus on resilience-promoting skills for the return to work. Women enrolled in the study will have access to e-mental health literacy materials (details provided below).

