**Psychological Wellbeing, Resilience and Stress-related Coping Style**		
Hospital Anxiety and Depression Scale (HADS) [74]	HADS is a 14-item screening tool composed of two subscales, one for anxiety and other for depression. High scores indicate the presence of a mood disorder. Instrument validated for the Portuguese population [75].	Pregnancy
Edinburgh Postnatal Depression Scale (EPDS) [76]	EPDS is a 10-item questionnaire that screens for depression in pregnant women and during the first postpartum year. Depressed women score high in EPDS. Instrument validated for the Portuguese population [77].	Postpartum
Kennerley Blues Scale (KBS) [9]	KBS is an 18-item screening tool for postpartum blues. Women are asked to rate current emotions according to how different they feel compared to usual. It is composed of seven clusters: primary blues, reservation, hypersensitivity, depression, despondency, retardation, and decreased self-confidence.	Postpartum
Connor–Davidson Resilience Scale (CD-RISC) [78]	The original CD-RISC is a 25-item scale that measures resilience as the ability of overcoming adversity and stress coping ability. Two shorter versions of this scale are authorized for use, CD-RISC-10 and CD-RISC-2. CD-RISC-25 [79] and CD-RISC-10 [80] have been validated for the Portuguese population. In this study, either the CD-RISC-10 or the CD-RISC-2 (to be validated in this study if applicable) will be used.	Pregnancy Postpartum
Stress-Related Coping Style (BRIEF COPE) [81]	The BRIEF COPE characterizes coping styles and strategies following Lazarus & Folkman’s model [82] and the behavioral self-regulation model.	Pregnancy Postpartum
Self-Report on Happiness [83]	Self-report single-item on happiness to be measured in a daily basis via the smartphone application.	Pregnancy Postpartum

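### By Table 1, the only scale described as having a general anxiety subscale (HADS) is used in pregnancy only, so no general anxiety score is planned postpartum or after block 2

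*Protocol article*

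**What the plan says.** All references are to the protocol article.

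- **Outcome.** Section 2.4 lists psychological wellbeing among the main outcomes, covering mood and anxiety disorders, and names HADS and EPDS jointly as its instruments.
- **Instruments.** Table 1 says "HADS is a 14-item screening tool composed of two subscales, one for anxiety and other for depression" and gives its timing as pregnancy. It says "EPDS is a 10-item questionnaire that screens for depression in pregnant women and during the first postpartum year" and gives its timing as postpartum.
- **Assessment moments.** Section 2.4 sets a baseline (t0) at 28–30 weeks, followed by "one week after enrolment (t_1_; 29–31 gestation weeks), two weeks postpartum (t_2_), five months postpartum (t_3_), and twelve months postpartum (t_4").
- **Intervention.** Section 2.3 describes a 20-hour group programme "to be delivered in two blocks, one immediately before delivery and the other before returning to work". On the sessions: "The first block will consist of two sessions, four hours each, whereas the second block will be organized into three sessions, four hours each". On content: "Block 2 will recap the main contents of block 1 and focus on resilience-promoting skills for the return to work".
- **Aim.** Section 1.2 states the first aim as "to promote perinatal mental health, from the last trimester of pregnancy up to the first 12 months after childbirth".
- **Sample size and analysis.** Section 2.2 says that the sample is large enough to detect a medium effect on depression and anxiety scores. Section 2.5 plans a mixed model for repeated measures for main and secondary outcomes.

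**The concern.** The outcome definition, the aim and the sample-size text all treat anxiety as something on which the trial will report an intervention effect. The timing column of Table 1 stops the anxiety measurement before most of the intervention has been given, and before birth. The instrument that takes over after birth is described as covering depression only.

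What is at stake is whether the trial can say if the complete programme changes anxiety, including around the return to work, which is the focus of block 2. There is also a risk in reporting. A between-arm HADS difference at t1, about a week after baseline, could be presented as the programme's effect on anxiety when most of the programme had not yet been delivered. The repeated-measures model does not help, because HADS would supply at most one post-baseline value.

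**Working it through.** **1. Does the timing column distinguish the two periods?** Table 1 has 21 timing entries:

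| Timing in Table 1 | Entries |
|---|---|
| Pregnancy and postpartum | 6 (MHLS, CD-RISC, BRIEF COPE, happiness item, EASAVIC, biomonitoring) |
| Postpartum only | 14 (including EPDS, KBS, PBQ) |
| Pregnancy only | 1 (HADS) |

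6 + 14 + 1 = 21. The table marks both periods where both apply, so the single label for HADS carries meaning.

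**2. Which moments can carry HADS?** The pregnancy moments are t0 (28–30 weeks) and t1 (29–31 weeks). The postpartum moments are t2, t3 and t4. HADS is possible at no more than 2 of 5 moments, and at 0 of 3 postpartum.

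**3. Does another listed postpartum scale give a general anxiety score?**
- EPDS is described only as a screen for depression.
- The seven KBS clusters named in Table 1 do not include anxiety.
- PBQ has a subscale for anxiety about care, but it belongs to a bonding scale.

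No postpartum scale is described as giving a general anxiety score.

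**4. How many session hours come after the last possible HADS?**
- Block 1: 2 × 4 = 8 h
- Block 2: 3 × 4 = 12 h
- Total: 8 + 12 = 20 h, which matches the plan's figure.

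Block 2 recaps block 1 and prepares for the return to work, so it follows t1.
- If block 1 falls between t0 and t1: 12/20 = 60% of session hours come after the last HADS.
- If block 1 is held just before delivery, as section 2.3 literally says: 20/20 = 100%.

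The text does not settle which applies. The conclusion about block 2 is the same on both readings.

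**5. How long is the gap?** Time from t1 to t4, taking 12 months as 52 weeks:
- Birth at 37 weeks (the earliest retained, since preterm births are excluded): (37 − 31) + 52 = 58 to (37 − 29) + 52 = 60 weeks.
- Birth at 40 weeks: (40 − 31) + 52 = 61 to (40 − 29) + 52 = 63 weeks.

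**6. Which postpartum contact follows block 2?** Section 1.1 states: "Portuguese parents are also eligible for 120 or 150 days of paid leave at 100% and 80%, respectively". Assume that leave is counted from birth and is not extended. Then t3 falls at about 5/12 × 365 = 152 days, which is 152 − 120 = 32 days or 152 − 150 = 2 days after leave ends. At t4 the margin is 365 − 120 = 245 or 365 − 150 = 215 days. So t4 is the safer choice, and t3 leaves almost no margin for a woman on 150 days.

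**The case against.** The strongest objection is that the full schedule is not visible. Figure 1 is the schedule of enrolment, interventions and assessments. It is missing from the text at hand, and section 2.4 relies on it for the five moments. Section 2.4 calls Table 1 an overview, and the table never names t0 to t4. This stands as a limit on certainty, and the point is therefore made conditional on Table 1. If Figure 1 does place HADS postpartum, Table 1 is wrong and still needs correcting.

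Second, HADS before birth and EPDS after may be a deliberate pairing, since section 2.4 assigns mood and anxiety disorders to both. For depression that is reasonable, because both scales are described as covering it. For anxiety, the article describes no score from EPDS. It does not list the EPDS items either, so it cannot be said that EPDS carries no anxiety information at all.

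Two stronger readings are tempting and are not supported:
- *Anxiety is never measured after birth.* This is too broad. PBQ includes anxiety about care, and EPDS is nominally linked to anxiety. What is absent is a described general anxiety score.
- *A HADS result at t1 reflects at most block 1.* This treats the group sessions as the whole intervention. One arm also receives biofeedback, both intervention arms have mindfulness e-training online, and no start dates are given for either. Some of that exposure could precede t1. The 60% and 100% figures describe session hours, not total exposure.

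Finally, the loss is bounded. The figures used for the sample size are depression scores, and the other main outcomes keep their postpartum measurements.

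**Conclusion.** The point holds in a limited form. On Table 1 as printed, no general anxiety score is planned postpartum or after block 2, although anxiety disorders are part of a main outcome and the aim extends to 12 months after childbirth. General anxiety goes unscored for 58 to 63 weeks (births at 37 to 40 weeks), and at least 12 of 20 session hours fall in that interval. A HADS comparison at t1 would show only the effect of whatever sessions, e-training or biofeedback had begun by then.

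This assumes that Figure 1 does not schedule HADS differently and that EPDS is used as Table 1 describes it. Confidence is medium for the first reason. Conclusions about postpartum depression on EPDS, happiness and the mother–child outcomes are not touched. It is worth correcting before enrolment because the change is cheap and determines whether the trial can answer its anxiety question.

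**What to change.** - Change the HADS timing in Table 1 to pregnancy and postpartum, and make Figure 1 agree.
- Keep HADS at t0 as baseline. Add HADS, or at least its anxiety subscale, at t2 and at t4. A woman who has not completed block 2 by t4 should be identified as such.
- State the gestational weeks of block 1. If it falls after t1, treat t1 as a second baseline. If it falls between t0 and t1, correct the description in section 2.3 that places it just before delivery.
- Describe any HADS comparison at t1 as an early-exposure result.

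**Cost.** Protocol wording, plus 2 × 14 = 28 items per woman for the full scale, fewer if only the anxiety subscale is used. No new visit and no moved assessment date. The downside is some added questionnaire burden at existing contacts, in a trial that expects about 40% attrition.

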In the first few days after childbirth, approximately 50% of recent mothers are likely to experience postpartum blues [3], which is mainly characterized by transient mild mood disturbance and tearfulness [4,9]. Postpartum blues symptomatology tends to disappear within approximately ten days after childbirth and no medical intervention is usually required [4]. Despite being a common non-pathological condition, postpartum blues has been associated to the onset of postpartum depression (PPD) [3,10,11]. PPD is the most common mental disorder diagnosed among women during the perinatal period [1,12], with an estimated prevalence of 13–19% [13]. PPD symptomatology is indistinguishable from any other non-psychotic major depression episode at a different stage in a woman’s life, the only difference being the onset, as acknowledged in DSM-5 [14]. Depressed parturients experience depressed mood most of the day or loss of interest and pleasure in usual activities, in combination with at least four of the following symptoms: significant weight loss or weight gain, insomnia or hypersomnia, psychomotor agitation or retardation, fatigue or loss of energy, feelings of worthlessness or excessive guilt, diminished ability to think or concentrate, and recurrent thoughts of death or suicide [14]. The onset of PPD is influenced by several factors, such as history of mental disorders [3,4,15], perinatal body dissatisfaction [16], marital satisfaction [17], perceived social support through close relatives and friends [3], life events [15], pregnancy-related complications [15], and hormonal changes [4]. Given the multifactorial nature of PPD and its prevalence and severity, it is crucial to screen for mental disorders during pregnancy and within four weeks of delivery [14].

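### HADS, the only general anxiety measure, is scheduled in pregnancy only, so the trial as written cannot estimate a postpartum effect on anxiety, a named main outcome

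*Protocol article*

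**What the plan says.** Section 2.4 lists as main effectiveness outcomes "mood disorders and anxiety disorders, assessed by the Hospital Anxiety and Depression Scale/HADS and by the Edinburgh Postnatal Depression Scale/EPDS", along with other maternal and mother–child measures. Section 2.2 closes its sample-size paragraph by saying that the sample is large enough for a medium effect on depression and on anxiety scores. Section 1.2 sets the period of interest from the last trimester to 12 months after childbirth.

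Table 1 describes the instruments and gives each a timing label:

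- HADS: "HADS is a 14-item screening tool composed of two subscales, one for anxiety and other for depression". The row ends "Instrument validated for the Portuguese population [75]. Pregnancy", so its timing is pregnancy only.
- EPDS: "EPDS is a 10-item questionnaire that screens for depression in pregnant women and during the first postpartum year". The row ends "Instrument validated for the Portuguese population [77]. Postpartum", so its timing is postpartum only.
- CD-RISC, BRIEF COPE and the happiness item, in the same block, are labelled for both periods.
- KBS, the postpartum blues scale, is labelled postpartum.

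Section 2.4 fixes five assessment moments: t0 (28–30 weeks), t1 (29–31 weeks), "two weeks postpartum (t_2"), five months (t3) and twelve months (t4). Section 2.3 places the two intervention blocks, "one immediately before delivery and the other before returning to work".

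**The concern.** A main outcome has to be measured in the period the trial makes claims about. With HADS confined to t0 and t1, the plan promises an answer on anxiety, and claims adequate size for it, but schedules no general anxiety measurement after birth. The return to work, which is the trial's distinctive theme, would have no anxiety data at all. A later analysis plan cannot repair this, because the values will not exist.

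Two smaller timing questions arise in the same rows of Table 1. EPDS has no baseline, although the table itself describes it as usable in pregnancy. KBS cannot be given at a scheduled visit before two weeks, although the Introduction says "Postpartum blues symptomatology tends to disappear within approximately ten days after childbirth".

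**Working it through.** The main point rests on the schedule and not on a calculated figure, so the check sets the timing labels against the visits.

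**Anxiety**

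1. Pregnancy visits: t0 and t1, one week apart, the later at 31 weeks at most. HADS can fall only there.
2. Postpartum visits: t2, t3 and t4. HADS at these: 0 of 3.
3. Block 1 is two sessions of four hours (2 × 4 = 8 h). Block 2 is three sessions of four hours (3 × 4 = 12 h). The total is 20 h. Block 2 precedes the return to work and so follows birth. HADS after block 2: none. The 12 of 20 hours in block 2 have no subsequent anxiety measurement.
4. Section 2.2 removes dyads with birth before 37 weeks. In retained dyads the last HADS is therefore at least 37 − 31 = 6 weeks before delivery.
5. Other instruments: no other row of Table 1 describes a general anxiety measure. The PBQ has an anxiety-about-care subscale, which is narrower.
6. Size claim: with 53 women per arm, two-sided α = 0.05 (sidedness is assumed) and 80% power, the detectable standardised difference between two arms is (1.960 + 0.842) × √(2/53) = 0.54. That is near a medium effect, but it applies only to an outcome measured at the time of interest.

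**EPDS baseline**

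EPDS before delivery: 0 of 2 visits. If r is the correlation between baseline and follow-up (not given in the document, so assumed), adjustment leaves a residual variance factor of 1 − r², and the detectable difference becomes 0.544 × √(1 − r²).

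| r | 1 − r² | Variance cut | Detectable d at 53 per arm |
|---|---|---|---|
| 0.3 | 0.91 | 9% | 0.52 |
| 0.4 | 0.84 | 16% | 0.50 |
| 0.5 | 0.75 | 25% | 0.47 |
| 0.6 | 0.64 | 36% | 0.44 |

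These gains are relative to having no baseline covariate. The HADS depression score from pregnancy is available, so the net gain is smaller. For illustration, if that score correlates 0.4 with later EPDS and a baseline EPDS would correlate 0.6, replacing one by the other cuts residual variance by 1 − 0.64/0.84 = 24%, not 36%.

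Section 2.5 defines ITT as everyone allocated, with missing values filled by last observation carried forward. A woman lost before t2 has no EPDS value to carry forward, so that analysis cannot include her. Section 2.2 expects about 40% attrition but does not say when it occurs.

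**KBS**

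The first postpartum visit is at day 14. The protocol gives blues about 10 days. The visit falls about 14 − 10 = 4 days after that period.

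**The case against.** Several stronger readings are tempting, and the document does not support them.

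- *HADS is never taken after any intervention.* A reader might infer this from the timing of block 1. However, Table 1 gives only coarse labels, and Figure 1, the detailed schedule, is not shown. It may place block 1 between t0 and t1. Biomonitoring in the biofeedback arm also runs in pregnancy, so t1 may follow its start. What the text does support is no postpartum HADS and none after block 2.
- *HADS is the only anxiety measure of any kind.* The PBQ subscale means that it is the only general one.
- *EPDS without a baseline cannot answer the question.* Under randomisation, comparing arms at t2, t3 and t4 is valid without a baseline. Women with a depression diagnosis or a history of major depression are not enrolled, which may narrow baseline scores and lower r. The loss is in precision and in the workability of carrying values forward, not in validity. Nor does section 2.5 say that HADS and EPDS would be pooled as one repeated outcome.
- *KBS at two weeks measures nothing.* The ten days are approximate and a tendency, so some women may still have symptoms. KBS appears among the main-outcome tools only in the Abstract, not in section 2.4.
- *Work engagement and presenteeism need a baseline too.* These are secondary outcomes, the randomised comparison does not require it, and section 2.4 already collects job satisfaction before leave. This is a preference, not a defect.

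One might also say that the HADS label is loose shorthand. Neighbouring rows labelled for both periods make that unlikely. If it is shorthand, the cell still needs correcting. The conflict with sections 1.2, 2.2 and 2.4 stands in either case.

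**Conclusion.** The schedule contradicts the outcome list. Anxiety is a main outcome with a size claim and an aim that runs to 12 months, yet general anxiety is measured at 0 of 3 postpartum visits and not at all after block 2. No postpartum anxiety effect can be estimated as the plan is written. This conclusion depends only on the Table 1 labels and the five stated visits. It does not depend on where block 1 falls.

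The EPDS and KBS points are secondary. A baseline EPDS would cut residual variance by 16–36% if r lies between 0.4 and 0.6 (an assumption), compared with no baseline covariate, and by less once HADS depression is used. The KBS timing weakens a supporting scale.

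**What to change.** Change the HADS timing in Table 1 to cover both periods, with at least the anxiety subscale at t2, t3 and t4. Analyse that subscale by MMRM with its t0 value as covariate. If this is not wanted, withdraw postpartum anxiety as a main outcome and remove anxiety from the size statement in section 2.2. Check that Figure 1 agrees.

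In the same amendment:

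- Give EPDS at t0. This adds precision and supplies a value for women lost before t2 in the ITT analysis as stated. It is not an endorsement of carrying a pregnancy value forward.
- Collect KBS once through the project app within about ten days of birth, or do not use it as an outcome. Align the Abstract's outcome list with section 2.4.

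Cost: the full HADS at three existing visits is 3 × 14 = 42 items, and EPDS at baseline adds 10, so at most 52 self-report items per woman over the whole study. The 18 KBS items are moved or, if the later administration is kept, given once more. The planned questionnaire system and app can carry all of this. The remaining cost is a schedule amendment.
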